### Sample size

There are no registered or published randomized controlled trials (RCTs) comparing limited with extensive mesenteric resection in patients with CD. Our sample size calculation is based on the surgical recurrence in a retrospective study reported by Coffey et al. [9]. It is estimated that 30% of subjects undergoing an ileocolonic anastomosis with conventional limited mesenteric excision would develop surgical recurrence at 60 months after surgery. To detect a 20% decrease in the surgical recurrence rate after wide mesenteric excision with 80% power and 5% significance, a total of 100 patients must be recruited. The sample size is adjusted to 116 to allow for a 10% loss to follow-up and 5% anastomotic leak.

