### Statistical analysis

Data will be presented as median (range), mean, and standard deviation for continuous variables, and percentages for categorical and ordinal data. In order to test whether there are differences between the two groups in the reduction of the primary and secondary outcome, Student’s *t* tests will be performed for continuous variables and chi-square or Fisher’s exact test for categorical variables. Those variables in which statistically significant differences are found will be introduced in the analyses as covariates. Kaplan-Meier analysis with log-rank statistics will be used to assess event-free interval and Cox forward conditional proportional hazards for regression analysis. We plan intention-to-treat analysis of the primary outcome. The full analysis set and per-protocol set will be used for the assessment of efficacy. Interim analyses will be done annually for the first 5 years after index surgery, and the sample size would be adjusted accordingly. An interim analyses will be performed to see if the trial should be continued or stopped, and so it serves as a safeguard. If the outcomes are very poor, more than would be expected, a clear-cut trend towards increased severe morbidity (classed as Clavien-Dindo grade 3 or greater) in relation to either the control or test group, the trial would be stopped and the enrolled participants would have been followed for outcomes and the primary analysis would have focused on the mortality end point. Alternatively, if there was a clear difference between the two groups in terms of benefits for the test cohort, with statistically significant findings emerging on comparison of one group over another that support uncontestable differences between groups, then it might also be stopped and all enrolled participants will be followed for outcomes and the primary analysis will focus on the efficacy end point. Data will be monitored by the treating clinicians and external independent trial monitoring committee, and the principle investigator of each participative site will take overall responsibility. An external independent trial monitoring committee will also analyze interim anonymized outcome data. All analyses considered a *P* value of ≤ 0.05 as statistically significant.

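### 100 patients do not give 80% power for 30% versus 10% with two-sided 5% tests; they give about 71–73%, or 64% with Fisher's exact test

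*Protocol article*

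**What the plan says.** All the design inputs stand in the Sample size section of the protocol article. The control rate is given as follows: "It is estimated that 30% of subjects undergoing an ileocolonic anastomosis with conventional limited mesenteric excision would develop surgical recurrence at 60 months". The effect is "To detect a 20% decrease in the surgical recurrence rate after wide mesenteric excision", with no statement of whether the decrease is absolute or relative. The result is "with 80% power and 5% significance, a total of 100 patients must be recruited". The total is then raised for attrition: "The sample size is adjusted to 116 to allow for a 10% loss to follow-up and 5% anastomotic leak". This section names neither a test nor its sidedness.

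The Statistical analysis section sets a non-directional aim ("In order to test whether there are differences between the two groups in the reduction of the primary and secondary outcome") and names "chi-square or Fisher’s exact test for categorical variables". For the time to recurrence it adds that "Kaplan-Meier analysis with log-rank statistics will be used to assess event-free interval". The threshold for all analyses is a P "value of ≤ 0.05 as statistically significant". No one-sided hypothesis is declared anywhere in the article.

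**The concern.** For 30% versus 10%, two-sided 5% and 80% power, standard formulas give roughly 60 patients per arm, so 50 per arm looks too few. A figure near 50 is what a one-sided 5% calculation gives. The sample size and the analysis then appear to rest on different error rates.

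The assumed effect is already very large, with a hazard ratio of about 0.30. If power for that effect is nearer 70% than 80%, a non-significant result read against the printed 80% would be taken as stronger evidence against extensive excision than the design supports.

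**Working it through.** **Inputs.** From the Sample size section: p1 = 0.30, a decrease of 0.20 read as absolute (so p2 = 0.10), power 80%, significance 5%, total 100. From the Statistical analysis section: chi-square, Fisher's exact and log-rank tests at P ≤ 0.05. Assumption: 1:1 allocation (50 per arm), because the ratio is not stated. Quantiles: 1.960 (two-sided 5%), 1.645 (one-sided 5%), 0.842 (80% power).

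**1. Reproducing the plan's figure.** Pooled two-proportion formula, with mean rate 0.20:

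n per arm = [z_α √(2 × 0.20 × 0.80) + z_β √(0.30 × 0.70 + 0.10 × 0.90)]² / 0.20²

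- One-sided 5%: [1.645 × 0.5657 + 0.842 × 0.5477]² / 0.04 = 48.4, so 49 per arm, 98 in total. This matches 100; power at 50 per arm is 81.1%.
- Two-sided 5%: [1.960 × 0.5657 + 0.842 × 0.5477]² / 0.04 = 61.6, so 62 per arm, 124 in total. This does not match.

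**2. Other two-sided calculations for 80% power.**

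| Method | Per arm | Total |
|---|---|---|
| Unpooled: (1.960 + 0.842)² × 0.30 / 0.04 = 58.9 | 59 | 118 |
| Arcsine | 60 | 120 |
| Fisher's exact, by enumeration (79.97% at this size) | 68 | 136 |
| Continuity-corrected formula | 72 | 144 |

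For the log-rank test under proportional hazards, HR = ln(0.9)/ln(0.7) = 0.295 and ln(HR) = −1.219. The average event rate is (30% + 10%)/2 = 20%.

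- Schoenfeld: 4 × (1.960 + 0.842)² / 1.219² = 21.1 events; 21.1 / 0.20 = 106 patients.
- Freedman: (1.960 + 0.842)² × (1.295/0.705)² = 26.5 events; 26.5 / 0.20 = 133 patients.

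No two-sided method gives 100.

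**3. Power delivered, two-sided 5%, 30% versus 10%.**

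| Method | 50 per arm (100) | 58 per arm (116, none lost) |
|---|---|---|
| Pooled normal approximation | 71.1% | 77.5% |
| Uncorrected chi-square, exact enumeration | 73.4% | 79.7% |
| Log-rank, simulated | about 73% | about 79% |
| Fisher's exact, enumeration | 64.0% | 71.6% |

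The log-rank simulations used 20,000 runs, exponential times and complete 60-month follow-up. Repeated simulations gave 72.5–73.5% at 100 patients. Schoenfeld's approximation gives 77.8% at 100, still short of 80% and optimistic against the simulation; Freedman's gives 68.2%.

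**4. Effect detectable with 100 patients.** With the pooled approximation at 50 per arm, power is 81.0% for 30% versus 8% and 78.7% for 30% versus 8.5%. So 80% power exists only for a rate of about 8% in the extensive-excision arm.

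**5. Relative reading of the decrease.** 30% × 0.80 = 24%. Two-sided, 30% versus 24% needs 859 per arm, 1,718 in total; 100 patients give about 10% power. Only the absolute reading comes near 100.

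**The case against.** The strongest reply is that the article never writes "two-sided". Its objective is worded in terms of a reduction, and a one-sided 5% calculation does yield 98, easily rounded to 100. On that view the sum is right and only the sidedness is undeclared. It is true that two-sidedness is an inference here. It is the natural one: the tests named are two-sided as usually run, the analysis looks for differences between groups, and the Cessation of trial section allows stopping for differences of one group over another. If one-sided 5% was meant, the sample size and the analysis contradict each other, and the paragraph still needs correcting.

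A second reply is that 116 patients are randomized, with intention-to-treat analysis of the primary outcome. Patients with a leak would stay in, and those lost would contribute time to the log-rank test until censoring. With 58 per arm and an assumed 10% loss spread over 60 months, simulated log-rank power is about 77%. That narrows the practical shortfall to about 3 points on that analysis. It does not rescue the printed statement, which attaches 80% to 100 patients and reserves the other 16 for loss and leaks.

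Third, Fisher's test is the least favourable of the tests named, and the expected counts (about 10 events per arm) do not require it. That is fair: the 64% applies only if Fisher is chosen, but the article leaves that choice open.

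Finally, the article says the sample size would be adjusted at the annual interim analyses. It gives no rule for doing so, and this does not make the stated power of the planned size correct.

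**Conclusion.** The point holds. With the article's own inputs, 100 patients deliver about 71–73% power with the uncorrected chi-square or log-rank test and 64% with Fisher's exact test. The false-negative risk is therefore 27–36% against the stated 20%. For 80% power, 118–124 evaluable patients are needed for the chi-square test, 106–133 for the log-rank test depending on the approximation, and about 136 for Fisher's.

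This rests on an absolute reduction to 10% (the reading that favours the plan), 1:1 allocation, two-sided testing at 5% and, for the log-rank figures, exponential times with 60 months of follow-up.

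The figures allow nothing for the annual interim looks; adjusting for them would lower power further. They would also be lower if the trial closed five years after the first enrollment, as the Cessation of trial section provides, and late entrants were followed for less than 60 months.

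**What to change.** Rewrite the sample size paragraph so that inputs, test and power agree. For example: an absolute reduction in surgical recurrence from 30% to 10% at 60 months, two-sided alpha 0.05; 100 evaluable patients give about 71–73% power with the log-rank or uncorrected chi-square test; 116 patients analysed by intention to treat with complete follow-up give about 78–80%, and about 77% by log-rank if 10% are lost evenly over follow-up. Name the log-rank or uncorrected chi-square test as the basis of the calculation, not Fisher's.

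If a one-sided 5% test was intended, say so in both the Sample size and the Statistical analysis sections, and reconcile it with the non-directional comparisons described there.

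The cost is the wording of one paragraph and a less favourable stated power. No additional patients are requested.

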### Statistical analysis

Data will be presented as median (range), mean, and standard deviation for continuous variables, and percentages for categorical and ordinal data. In order to test whether there are differences between the two groups in the reduction of the primary and secondary outcome, Student’s *t* tests will be performed for continuous variables and chi-square or Fisher’s exact test for categorical variables. Those variables in which statistically significant differences are found will be introduced in the analyses as covariates. Kaplan-Meier analysis with log-rank statistics will be used to assess event-free interval and Cox forward conditional proportional hazards for regression analysis. We plan intention-to-treat analysis of the primary outcome. The full analysis set and per-protocol set will be used for the assessment of efficacy. Interim analyses will be done annually for the first 5 years after index surgery, and the sample size would be adjusted accordingly. An interim analyses will be performed to see if the trial should be continued or stopped, and so it serves as a safeguard. If the outcomes are very poor, more than would be expected, a clear-cut trend towards increased severe morbidity (classed as Clavien-Dindo grade 3 or greater) in relation to either the control or test group, the trial would be stopped and the enrolled participants would have been followed for outcomes and the primary analysis would have focused on the mortality end point. Alternatively, if there was a clear difference between the two groups in terms of benefits for the test cohort, with statistically significant findings emerging on comparison of one group over another that support uncontestable differences between groups, then it might also be stopped and all enrolled participants will be followed for outcomes and the primary analysis will focus on the efficacy end point. Data will be monitored by the treating clinicians and external independent trial monitoring committee, and the principle investigator of each participative site will take overall responsibility. An external independent trial monitoring committee will also analyze interim anonymized outcome data. All analyses considered a *P* value of ≤ 0.05 as statistically significant.

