### End points

In total, patients will be followed for 5 years after surgery. The primary end point of the study is postoperative surgical recurrence. Surgical recurrence is defined as the requirement for repeat surgery for a CD-related indication caused by recurrent disease in the same anatomical areas. If reoperation is required it should be documented whether the reason is a specific CD-related complication, or a complication related to surgery in general (i.e., hemorrhage, intraperitoneal collection not amenable to conservative treatment, wound dehiscence, anastomotic leakage). CD-related indications for surgery include: (1) development of symptoms refractory to medical treatment; and (2) development of a complication caused by CD (i.e., fistula, perforation, and obstruction).

Secondary end points include assessment of endoscopic recurrence and clinical recurrence. Endoscopic recurrence will be assessed using the widely accepted Rutgeert’s score [15]. Only disease (Rutgeert’s score i2, or higher) proximal to the anastomosis or in the perianastomotic area is considered to be consistent with endoscopic recurrence. Disease in other sites will not be considered to be recurrence. Clinical recurrence is defined as the presence of endoscopic disease or radiological evidence plus the presence of symptoms attributable to CD that are severe enough to require medical or surgical treatment.

In addition, intra-operative complications and 30-day postoperative outcomes will be evaluated. These include estimated blood loss, duration of surgery, postoperative morbidity, reoperation rate, and the length of postoperative hospital stay. Postoperative complications will be recorded and classified based on the Clavien-Dindo classification [16].

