### Cessation of trial

The trial will stop in three circumstances: (1) once 5 years after first enrollment has been reached; (2) statistically significant findings emerge on comparison of one group over another that support uncontestable differences between groups; and (3) a clear-cut trend is demonstrated toward increasingly severe morbidity (classified as Clavien-Dindo grade 3 or greater) in either treatment arm.

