### Trial status

The protocol reported here is version 1.2, dated 30 October 2018. Trial enrollment began on 1 February 2019 and is anticipated to finish on 31 December 2020.

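### Surgical recurrence has two unranked tests, chi-square or Fisher and log-rank; the log-rank test should be named as decisive, and the two follow-up rules reconciled

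*Protocol article*

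**What the plan says.** Under End points: "The primary end point of the study is postoperative surgical recurrence". The same section says "In total, patients will be followed for 5 years after surgery", and the Sample size section assumes that 30% of the limited-excision (LME) group "would develop surgical recurrence at 60 months after surgery".

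Under Statistical analysis, the tests are introduced with "In order to test whether there are differences between the two groups in the reduction of the primary and secondary outcome": t tests for continuous data, and chi-square or Fisher's exact test for categorical data. Surgical recurrence is a yes/no event, so on a plain reading it falls to chi-square or Fisher. The section continues "Kaplan-Meier analysis with log-rank statistics will be used to assess event-free interval" and adds Cox regression. It plans intention to treat for the primary outcome and sets P ≤ 0.05 for every analysis. It does not rank the tests.

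Two statements imply incomplete follow-up. Under Sample size: "The sample size is adjusted to 116 to allow for a 10% loss to follow-up and 5% anastomotic leak". Under Cessation of trial, the first stopping circumstance is "once 5 years after first enrollment has been reached". The Trial status section gives the dates: "Trial enrollment began on 1 February 2019 and is anticipated to finish on 31 December 2020".

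**The concern.** A test of proportions needs each patient's status at a common time. Patients lost before 60 months, or not yet there when the trial stops, have no known 60-month status. A two-by-two table can only remove them or enter them as event-free. Either choice misstates the 60-month risk. If loss differs between arms, the two choices bias the comparison in opposite directions. Kaplan-Meier and log-rank methods use each patient's observed time and are already in the plan.

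There is also a multiplicity problem. With two or three tests of one end point at the same threshold and none ranked, the deciding test can be chosen after the results are known.

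**Working it through.** **Inputs.** 30% recurrence at 60 months with LME, 80% power, 5% significance, 100 patients raised to 116, 10% loss (Sample size); enrolment dates (Trial status); stop rule (Cessation of trial). Assumptions: 1:1 allocation, constant hazards, uniform entry, and the 20% decrease read as 20 percentage points (30% vs 10%). A relative reading, 30% vs 24%, would need 1,718 patients two-sided.

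**1. The plan's own figure.** For two proportions, n per arm = [z_α√(2·0.2·0.8) + 0.842√(0.3·0.7 + 0.1·0.9)]² / 0.2².
- One-sided 5%: (1.645·0.566 + 0.842·0.548)²/0.04 = 48.4, so 49 per arm, 98 in total.
- Two-sided 5%: (1.960·0.566 + 0.842·0.548)²/0.04 = 61.6, so 62 per arm, 124 in total.

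Of the variants tried (pooled, unpooled, arcsine, continuity-corrected, log-rank; one- and two-sided), only the one-sided pooled formula comes within 3% of 100. The step to 116 is in order: 100 × 1.10 × 1.05 = 115.5, and 100/(0.90 × 0.95) = 117.

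**2. Length of follow-up.** 1 February 2019 to 31 December 2020 is 23 months. Stopping 60 months after the first enrolment leaves 60 − 23 = 37 months for the last patient, so follow-up spans about 37–60 months. Under the End points section every retained patient reaches 60.

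**3. Crude rates if incomplete patients count as recurrence-free.** The 60-month cumulative hazards are −ln 0.7 = 0.357 (LME), −ln 0.9 = 0.105 (extensive excision, EME) and −ln 0.9 = 0.105 (10% loss). The observed risk is λ/(λ+μ) × [1 − e^−(λ+μ)].
- Five years per patient: LME 0.357/0.462 × (1 − 0.7·0.9) = 28.6%; EME 0.5 × (1 − 0.9·0.9) = 9.5%. Simulation gives 28.5% vs 9.4%, a difference of about 19 points.
- Calendar stop: averaging 1 − e^−λu over 37–60 months gives 25.0% and 8.2% before loss. With 10% loss, simulation gives 24.0% and 7.8%, about 16 points.

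**4. Crude rates if lost patients are dropped** (five years per patient). LME 0.286/(0.286 + 0.7·0.9) = 31.2%; EME 0.095/(0.095 + 0.81) = 10.5%. The error now goes upward.

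**5. Unequal loss with no true effect** (30% in both arms, loss 0% LME and 20% EME, full follow-up). The loss hazard in EME is −ln 0.8 = 0.223.
- Counted recurrence-free: EME 0.357/0.580 × (1 − 0.7·0.8) = 27.1% vs 30.0%, a false benefit of about 3 points.
- Dropped: EME 0.271/(0.271 + 0.56) = 32.6% vs 30.0%, a false harm of similar size.

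**6. Error rates and power** (simulation, 10,000–20,000 runs, 58 per arm unless stated; lost patients counted as recurrence-free; type I rows with full follow-up unless stated).

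| Setting | Chi-square | Log-rank | Either | Fisher |
|---|---|---|---|---|
| Type I, loss 10%/10% | 5.0% | 4.9% | 5.7% | – |
| Type I, loss 5%/15% | 5.6% | 5.0% | 6.5% | – |
| Type I, loss 0%/20% | 6.4–6.9% | 5.0–5.2% | 7.8–8.2% | – |
| Type I, loss 0%/20%, calendar stop | 5.9% | 5.0% | – | – |
| Power, calendar stop, 10% loss | 68–69% | 68–69% | – | 58% |
| Power, full follow-up, no loss, 50 per arm | 73% | 72–73% | – | 64% |

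**7. Size for a two-sided log-rank test.** HR = ln 0.9/ln 0.7 = 0.295. Schoenfeld: 4(1.960 + 0.842)²/(ln 0.295)² = 21.1, so 22 events. Freedman: (1.960 + 0.842)² × (1.295/0.705)² = 26.5, so 27 events. At a mean risk of 20% these are 110 and 135 patients. With 116 patients, power is 84% (Schoenfeld) or 79% (simulation) with full follow-up and no loss, 77% (simulation) with 10% loss, and 69% under the calendar stop with 10% loss.

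**The case against.** The strongest reply is that the section lists methods by data type and that surgical recurrence, with a defined start and an event that ends participation, is naturally the event-free interval. Log-rank may already be the intended test, and a condensed article may leave the ranking and the handling of losses to a full protocol or SAP not shown here. It is right that the absence of a missing-data rule is no finding in itself. But the article does more than omit detail: it names, for the primary outcome, a test that cannot handle censoring, and sets a competing test beside it at the same threshold.

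Three stronger readings are tempting and are not supported.

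- A reader might infer that the plan counts lost or incompletely followed patients as recurrence-free. No section says so. The inflation from 100 to 116 suggests, if anything, that they leave the denominator.
- A reader might blame the test for the whole shrinkage from 20 to 16 points. With 5 years per patient the difference is still about 19 points, so roughly 3 of the 4 lost points come from the conflict over follow-up.
- A reader might take 64% vs 72% power as the price of ignoring censoring. Chi-square reaches 73% in that setting; the gap is Fisher's conservatism.

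The 8% error rate needs 0% vs 20% loss. Nothing in the document suggests this; patients are blinded and reviewed every 6 months.

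**Conclusion.** The point stands as one of an unranked pair of tests, one of them poorly suited to incomplete follow-up. It should be corrected, but it does not invalidate the trial. With similar loss in both arms, chi-square and log-rank have nearly the same type I error (about 5%) and power. The harm is fourfold: 60-month rates and their difference are misstated; bias runs in a direction set by an unstated rule if loss differs by arm; 8–10 points of power go if Fisher's test is used; and there is room to choose a test afterwards, worth about 1.5 points of type I error at 5%/15% loss and about 3 in the stress case.

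The figures rest on 1:1 allocation, constant hazards, uniform entry, a 20-point absolute effect and loss unrelated to prognosis. The log-rank test also needs that last assumption. It does not restore information lost to an earlier stop.

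**What to change.** 1. Name one primary analysis: a two-sided log-rank test of time from ileocolic resection to surgical recurrence, by intention to treat, censored at last contact, reported with the Kaplan-Meier 60-month risk difference and its 95% CI. Label Cox and any other analysis of this end point as supportive.
2. Keep chi-square or Fisher for outcomes observed in full, such as 30-day morbidity.
3. Reconcile End points (5 years per patient) with Cessation of trial (5 years from first enrolment), so that the follow-up available to the primary analysis is fixed.
4. Restate the power of the 116 patients for the two-sided log-rank test under the reconciled follow-up, since the stated 100 fits only a one-sided comparison of proportions.

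Items 1 and 2 are changes of wording, with no new data and no analysis not already planned. Item 4 is a short recalculation. Item 3 may lengthen follow-up, depending on which statement the sponsor keeps.

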### Maintenance therapy

Prophylactic treatment is recommended after ileocolic intestinal resection in patients with at least one risk factor for recurrence (Table 1) [14]. For those developing endoscopic recurrence or clinical recurrence after surgery, management will be undertaken in keeping with local gastroenterology standard practice and guidelines.

**Table 1 Tab1:** Predictors of early postoperative recurrence after ileocolonic resection

Risk factor	Level of evidence
Smoking	EL1
Prior intestinal surgery	EL1
Penetrating disease at index surgery	EL2
Perianal location	EL2
Granulomata in resection specimen	EL2
Myenteric plexitis	EL3

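### Covariates are chosen by between-group significance, and a forward conditional Cox model does not protect the treatment term, so the adjusted hazard ratio could be attenuated or go unreported

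*Protocol article*

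**What the plan says.** All the relevant rules stand in the Statistical analysis section of the protocol article.

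- The group comparisons (t tests, chi-square or Fisher's exact test) are introduced with "In order to test whether there are differences between the two groups in the reduction of the primary and secondary outcome". Baseline variables are not mentioned.
- The next sentence gives the covariate rule: "Those variables in which statistically significant differences are found will be introduced in the analyses as covariates".
- For time to event, "Kaplan-Meier analysis with log-rank statistics will be used to assess event-free interval", and the regression method is "Cox forward conditional proportional hazards for regression analysis". Whether treatment is kept in that model is not said.
- The principle for the main comparison is "We plan intention-to-treat analysis of the primary outcome". Which test or model is primary is not stated.

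Three other sections bear on the point. Under End points, "Secondary end points include assessment of endoscopic recurrence and clinical recurrence", and clinical recurrence is defined to include symptoms needing medical or surgical treatment. The Discussion says that endoscopic and clinical recurrence are associated with reoperation. Under Maintenance therapy, Table 1 lists six "Predictors of early postoperative recurrence after ileocolonic resection".

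**The concern.** The covariate rule can be read in two ways, and neither is sound.

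**Literal reading.** The variables tested are outcomes, so an outcome that differs between arms becomes a covariate. Endoscopic recurrence is a likely candidate: the Background reports preliminary data in which extensive excision lowered it, so the investigators expect a difference. If the operation prevents reoperation partly by preventing endoscopic recurrence, adjusting for that recurrence removes part of the effect under study. Clinical recurrence is worse placed still, because its definition overlaps the primary end point.

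**Baseline reading.** In a randomized trial, a significance test between arms at baseline detects chance. It does not show which variables predict reoperation, so the rule selects on the wrong property.

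**Forward selection.** If treatment has to pass the entry test like any other term, a hazard ratio with its interval appears only when significant. It is then selected toward large effects, and the usual interval does not allow for the selection. If treatment fails the test, the trial has no adjusted estimate.

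**Working it through.** The disputed rule has no figure of its own to reproduce. The check takes the number of events from the sample-size section and then simulates the two rules.

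**1. Reading the design effect.** The Sample size section says "It is estimated that 30% of subjects" in the control arm have surgical recurrence at 60 months. It asks for a 20% decrease with 80% power at 5% significance, giving 100 patients. With an absolute decrease (30% v 10%), a pooled two-proportion formula and a one-sided test:

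n per arm = [1.645·√(2·0.2·0.8) + 0.842·√(0.3·0.7 + 0.1·0.9)]² / 0.20² = 48.4, so 49 per arm, 98 in total.

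This is close to 100. The two-sided version gives 124. A relative 20% (30% v 24%) would need 1,352 one-sided or 1,718 two-sided, so the absolute reading is used.

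**2. Expected events (equal allocation assumed).**
- N = 100: 50·0.30 + 50·0.10 = 20.
- N = 116: 58·0.30 + 58·0.10 = 23.2.
- If the trial stops 5 years after first enrollment (Cessation of trial), with uniform entry over about 23 months, mean follow-up is 60 − 11.5 = 48.5 months. With constant hazards the risks are 1 − exp(−0.357·48.5/60) = 25.0% and 1 − exp(−0.105·48.5/60) = 8.2%. N = 100 then gives 50·(0.250 + 0.082) = 16.6.

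Implied hazard ratio = ln(0.90)/ln(0.70) = 0.295.

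**3. Simulation of the stated rules.** There were 1,000 trials per scenario with N = 100 and 60-month risks of 30% v 10%. Six binary baseline covariates had prevalence 40%, two of them prognostic with log hazard ratio 0.5. Covariates and endoscopic recurrence were screened between arms at p ≤ 0.05. Forward Cox selection used entry 0.05 and removal 0.10. The endoscopic rates, their hazard ratios for reoperation, and the covariate number, prevalence and strength are assumptions. Endoscopic recurrence was simplified to a fixed yes/no factor acting from surgery.

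| Endoscopic recurrence, control v extensive; its HR for reoperation | Passes the screen | Median treatment HR, unadjusted | Median treatment HR, adjusted* | Log-rank power | Adjusted power* | Treatment omitted by forward selection |
|---|---|---|---|---|---|---|
| 60% v 60%; HR 1 (no role) | 5% | 0.29 | 0.29 | 72% | 68% | 28% |
| 60% v 35%; HR 4 | 76% | 0.29 | 0.37 | 72% | 43% | 49% |
| 60% v 25%; HR 4 | 94% | 0.30 | 0.46 | 71% | 27% | 66% |
| 60% v 25%; HR 8 | 96% | 0.28 | 0.51 | 74% | 16% | 78% |

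*Treatment kept in, plus every covariate that passed the screen.

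The adjusted columns show that keeping treatment in the model does not cure the attenuation; variables measured after randomization must also be kept out.

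**4. Null case.** With no treatment effect and no role for endoscopic recurrence, the adjusted test rejected in 3.5% of trials and the log-rank test in 4.1%. The Monte Carlo standard error is about √(0.04·0.96/1000) = 0.6 points.

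**The case against.** **The literal reading is implausible.** It would make the primary outcome its own covariate, which points to loose wording in a condensed article. The abstract also lists demographics and risk factors among the data collected. This stands as far as it goes: outcome adjustment is possible under the text, not certain. But the alternative reading is also a poor rule, and the article states the rule rather than leaving it open.

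**The main comparison is untouched.** This stands in full. The chi-square/Fisher and log-rank comparisons under intention to treat do not use the covariate rule, and the sample size rests on proportions. A reader might infer that the trial's main result would be invalid; the documents do not support that. Equally, they do not say that the Cox model is only supportive.

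**Treatment as a selection candidate is an inference.** This also stands. The article is silent, and the analysts may intend to force treatment in. Where endoscopic recurrence has no role, the 28% omission rate is simply the complement of 72% power, so little is lost as a test. What is lost is the estimate and its interval.

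**Stronger inferences that fail.**
- *Inflated type I error:* the null simulation is, if anything, slightly conservative.
- *A high chance of spurious imbalance across all six Table 1 factors:* granulomata and myenteric plexitis are read from the resected specimen, after allocation, and prior intestinal surgery should be uncommon in patients having their index resection.
- *Too few events for seven model terms:* the rule offers only variables that differ between arms, on average 6·0.05 = 0.3 of six by chance.
- *Neglect of Table 1:* that table guides prophylaxis, and a covariate list may sit in an analysis plan not shown.

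**Conclusion.** The concern holds for the adjusted Cox estimate. As written, the two rules allow adjustment for an outcome on the way to reoperation and do not secure a reported treatment hazard ratio. On the baseline reading they choose covariates for the wrong reason, although the simulation shows no shift in the median hazard ratio in that case.

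The size depends on inputs that the documents do not give. Under the assumed endoscopic rates and hazard ratios, a true effect near 0.29 would appear as 0.37 to 0.51, with adjusted power of 16% to 43% against 71% to 74% for the log-rank test. Omission of treatment in 49% to 78% of trials further assumes that treatment is subject to selection. These figures illustrate the mechanism and do not forecast this trial. With roughly 17 to 23 events, there is little information to support any model search.

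**What to change.** Replace the covariate and Cox sentences with text to this effect:

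- The primary analysis is the unadjusted log-rank test of surgical recurrence, by intention to treat.
- A supportive Cox model always includes treatment and at most two factors known before randomization and fixed in advance, for example smoking and perianal disease from Table 1.
- No covariate is chosen by a between-group test or by forward selection.
- No variable measured after randomization enters the model. Since the envelope is opened during the operation, this rules out specimen findings as well as recurrence outcomes.

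The cost is wording only: the sample size and trial conduct do not change, and risk factors are already to be assessed. It should be settled before the first of the annual interim comparisons. The downside is that with so few events even a short fixed covariate list gives an imprecise adjusted estimate, which is why that model should stay supportive.
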